## Abstract

**Background:**

Lifestyle behavior change and mindfulness have direct and synergistic effects on cognitive functioning and may prevent Alzheimer disease and Alzheimer disease–related dementias (AD/ADRD). We are iteratively developing and testing My Healthy Brain (MHB), the first mindfulness-based lifestyle group program targeting AD/ADRD risk factors in older adults with subjective cognitive decline. Our pilot studies (National Institutes of Health [NIH] stage 1A) have shown that MHB is feasible, acceptable, and associated with improvement in lifestyle behavior and cognitive outcomes.

**Objective:**

We will compare the feasibility of MHB versus an education control (health enhancement program [HEP]) in 50 older adults (aged ≥60 y) with subjective cognitive decline and AD/ADRD risk factors. In an NIH stage 1B randomized controlled trial (RCT), we will evaluate feasibility benchmarks, improvements in cognitive and lifestyle outcomes, and engagement of hypothesized mechanisms.

**Methods:**

We are recruiting through clinics, flyers, web-based research platforms, and community partnerships. Participants are randomized to MHB or the HEP, both delivered in telehealth groups over 8 weeks. MHB participants learn behavior modification and mindfulness skills to achieve individualized lifestyle goals. HEP participants receive lifestyle education and group support. Assessments are repeated after the intervention and at a 6-month follow-up. Our primary outcomes are feasibility, acceptability, appropriateness, credibility, satisfaction, and fidelity benchmarks. The secondary outcomes are cognitive function and lifestyle (physical activity, sleep, nutrition, alcohol and tobacco use, and mental and social activity) behaviors. Data analyses will include the proportion of MHB and HEP participants who meet each benchmark (primary outcome) and paired samples 2-tailed *t* tests, Cohen *d* effect sizes, and the minimal clinically important difference for each measure (secondary outcomes).

**Results:**

Recruitment began in January 2024. We received 225 inquiries. Of these 225 individuals, 40 (17.8%) were eligible. Of the 40 eligible participants, 21 (52.5%) were enrolled in 2 group cohorts, 17 (42.5%) were on hold for future group cohorts, and 2 (5%) withdrew before enrollment. All participants have completed before the intervention assessments. All cohort 1 participants (9/21, 43%) have completed either MHB or the HEP (≥6 of 8 sessions) and after the intervention assessments. The intervention for cohort 2 (12/21, 57%) is ongoing. Adherence rates for the Garmin Vivosmart 5 (128/147, 87.1% weeks) and daily surveys (105/122, 86.1% weeks) are high. No enrolled participants have dropped out. Enrollment is projected to be completed by December 2024.

**Conclusions:**

The RCT will inform the development of a larger efficacy RCT (NIH stage 2) of MHB versus the HEP in a more diverse sample of older adults, testing mechanisms of improvements through theoretically driven mediators and moderators. The integration of mindfulness with lifestyle behavior change in MHB has the potential to be an effective and sustainable approach for increasing the uptake of AD/ADRD risk reduction strategies among older adults.

**Trial Registration:**

ClinicalTrials.gov NCT05934136; https://www.clinicaltrials.gov/study/NCT05934136

**International Registered Report Identifier (IRRID):**

DERR1-10.2196/64149

## Introduction

### Background

Alzheimer disease and Alzheimer disease–related dementias (AD/ADRD) are debilitating neurodegenerative disorders that impair cognitive and daily functioning [1]. An estimated 50 million people are living with AD/ADRD worldwide, with 10 million new cases occurring annually [2-4]. AD/ADRD places an immense burden on individuals, families, and health care systems. The economic toll of family and unpaid caregiving for AD/ADRD was US $346.6 billion in 2023 [5]. In the early stages of AD/ADRD, approximately half of adults aged ≥65 years perceive subjective cognitive decline (SCD) [6,7] in memory or other cognitive domains before neurodegeneration can be detected through cognitive testing [8,9]. SCD is associated with a greater likelihood of underlying AD/ADRD biomarker pathology and increased risk for future cognitive decline and AD/ADRD [10-13]. This preclinical stage is a critical window to engage older adults in preventive interventions that aim to modify AD/ADRD risk factors.

Growing research indicates that multiple lifestyle behaviors are important for AD/ADRD prevention [14-21]. In 2020, the Lancet Commission on Dementia identified 12 modifiable risk factors accounting for 40% of AD/ADRD cases worldwide: less education, hypertension, hearing impairment, smoking, obesity, depression, physical inactivity, diabetes, low social contact, excessive alcohol consumption, a history of head injury, and exposure to air pollution [22]. The commission also highlighted the need for further research on additional lifestyle risk factors such as poor sleep [23-25], diet [23,26], and mental activity [27,28], which may influence AD/ADRD risk but have shown mixed findings [29]. Multidomain trials targeting modifiable lifestyle risk factors identified in the *Lancet* report have demonstrated the potential to improve cognition among older adults with early cognitive decline [30,31]. However, not all multidomain trials have reported positive results [32-34]. Trials have also failed to modify behaviors [33], or they have inconsistently reported lifestyle outcomes [30]. Complex and time-intensive intervention designs hindered participant adherence [35,36] and limit future implementation. Additional research is needed to develop more effective and practical interventions that promote sustained engagement and adherence to AD/ADRD prevention strategies among older adults.

Mindfulness practices may help address challenges in modifying lifestyle behaviors and offer direct brain health benefits. Mindfulness is commonly defined as the practice of nonjudgmental awareness of the present moment [37]. Mindful self-regulation theory suggests that mindfulness involves several self-regulation processes (eg, emotion regulation, cognitive control, and self-monitoring) that enhance one’s ability to cope with urges (eg, overeating or avoiding exercise) and make healthier lifestyle choices [38-40]. Mindfulness practice is positively associated with measures of enhanced brain structure [41-43] and cognitive function [41,44-48]. In addition, mindfulness is associated with reductions in psychological symptoms, such as depression, anxiety, and attitudes and worries regarding AD/ADRD [49-52], which are independent risk factors for AD/ADRD [53-56] and an inactive lifestyle [57]. Mindfulness is feasible and acceptable for older adults, including individuals with SCD [38,52,58]. Prior research suggests that cognitive benefits associated with mindfulness can be observed with brief practice [59-61], suggesting that mindfulness is amenable to time-limited interventions. Despite these advantages, mindfulness has been overlooked in behavior modification AD/ADRD prevention interventions.

Our interdisciplinary team has developed the first group mindfulness-based lifestyle intervention (My Healthy Brain [MHB]) that aims to modify early risk for AD/ADRD. We conducted a series of preliminary studies to develop MHB following the National Institutes of Health (NIH) Stage Model [62], an iterative framework for guiding behavioral intervention development and testing, from pilot studies to implementation and dissemination (Figure 1). First, our systematic review and meta-analysis (we analyzed 79 studies with 9233 participants) found moderate- to high-quality evidence that mindfulness-based interventions were associated with significant improvements in multiple lifestyle behaviors linked to brain health, including sleep, physical activity, alcohol use, and tobacco cessation [63]. Second, we conducted iterative studies of older adults with AD/ADRD risk factors to determine the best delivery modality and strategies to incorporate mindfulness into lifestyle behaviors. Preliminary studies included (1) an in-person clinical pilot (N=24) [64], (2) a telehealth group case series (N=7) [65], and (3) a mixed methods study to adapt the program via qualitative focus groups (N=11) and conduct a feasibility pilot with exit interviews (N=10) [66]. MHB met benchmarks set a priori for feasibility, credibility, satisfaction, and safety (there were no adverse events). We observed preliminary improvements (moderate to large effects) in subjective and objective measures of cognitive function, physical activity, sleep, and proposed mechanisms. Exit interviews confirmed the satisfaction with mindfulness and feasibility with technologies to support behavior change (monitoring steps via an activity watch) and remote delivery (Zoom; Zoom Video Communications, Inc). Finally, we conducted a qualitative study with health care professionals caring for older patients (N=26) to address barriers to implementing study procedures (eg, recruitment, enrollment, and retention) and maximizing diversity to prepare for the first feasibility randomized controlled trial (RCT) of MHB [67].

**Figure 1 figure1:**
[figure not shown]
Iterative development of My Healthy Brain (MHB) following the National Institutes of Health Stage Model. The current feasibility randomized controlled trial (RCT; starred box) will inform an efficacy RCT (dashed box). HEP: health enhancement program.

### Objectives

Building upon our preliminary studies, we report on the improved protocol and initial launch of the first feasibility RCT of MHB (NIH stage 1B). We are enrolling 50 older adults (aged ≥60 y) with SCD and modifiable AD/ADRD lifestyle risk factors. Participants are randomized to MHB or a time- and attention-matched education control (health enhancement program [HEP]) [68,69], both delivered in telehealth groups over 8 weeks. The primary aim is to assess the feasibility, acceptability, appropriateness, credibility, satisfaction, and fidelity of MHB against established Go–No-Go benchmarks [64,70-74]. The secondary aim is to investigate preliminary improvements in cognitive and lifestyle outcomes and engagement in proposed mechanisms. The results will inform the first efficacy RCT of MHB and mechanistic testing of cognitive and lifestyle outcomes.

## Methods

### Overview

We are conducting a virtual, single-blind, feasibility RCT of the MHB intervention versus the HEP [68,69] education control (N=50). Our study is consistent with the research objectives and activities specified in stage 1B of the NIH Stage Model [62]. NIH stage 1 focuses on intervention development, testing, refinement, and modification. NIH stage 1B activities emphasize the refinement of intervention and training materials, feasibility and pilot testing, and early attention to implementation. As such, our study is designed to confirm the feasibility of MHB and assess engagement in intervention outcomes and hypothesized mechanisms before conducting a fully powered efficacy RCT [75-77]. All procedures described herein are conducted fully remotely, allowing for both local and national recruitment. We followed the National Council on Aging guidelines for using technology with older adults [78] and our established digital health trials [66,70,74,79-92]. Figure 2 presents the study flow.

We preregistered our RCT on ClinicalTrials.gov (NCT05934136) before enrolling the first participant.

**Figure 2 figure2:**
[figure not shown]
Study flow and timeline. Color key: yellow=recruitment, green=assessment, and blue=programs. BRANCH: Boston Remote Assessment for Neurocognitive Health; Garmin: Garmin Vivosmart 5 watch; HEP: health enhancement program; MHB: My Healthy Brain; RBANS: Repeatable Battery for the Assessment of Neuropsychological Status; SCD: subjective cognitive decline.

### Ethical Considerations

The Mass General Brigham (MGB) institutional review board (IRB) approved all study procedures (2023P001770). All participants review and sign written informed consent with a clinical research assistant (RA) before completing study procedures. Consent informs participants that, with any group-based intervention, there may be confidentiality and privacy risks. To minimize these risks, we discuss the importance of confidentiality at the start of each group; request that participants attend the session from a private location; and all data are deidentified, maintained in a secured location, and only accessed by IRB-approved members of the research team. Participants are compensated up to US $220: US $30 for before the intervention assessments, US $60 for after the intervention assessments, US $90 for 6-month follow-up assessments, with an additional US $40 for 7 out of 7 valid days of Garmin Vivosmart 5 wear during the before the intervention assessment period. This compensation strategy is meant to optimize participant engagement and motivation for 6-month follow-up assessments.

### Participants

Participants are older adults (aged ≥60) who are at early risk for AD/ADRD as determined by the presence of SCD [8], have no cognitive impairment (Telephone Interview for Cognitive Status score >30) [93], and have modifiable AD/ADRD risk factors (Cardiovascular Risk Factors, Aging, and Incidence of Dementia [CAIDE] score ≥6) [94,95]. Textbox 1 shows our full inclusion and exclusion criteria and rationales, which we have refined through our previous pilot studies [64-66]. These eligibility criteria were informed by similar lifestyle AD/ADRD prevention trials [30,31,35] and behavioral interventions for older adults [74,81,83,92,96].

Study inclusion and exclusion criteria with rationales.
**Inclusion criteria and brief rationales**
Aged ≥60 years: study populationSubjective cognitive decline (SCD; eg, forgetting information, getting lost, and repeating oneself): SCD Initiative criteria [8]Cardiovascular Risk Factors, Aging, and Incidence of Dementia score ≥6 [94,95]: modifiable Alzheimer disease and Alzheimer disease–related dementias (AD/ADRD) risk factors [30,35]Telephone Interview for Cognitive Status score >30 [93]: absence of AD/ADRD that would prevent meaningful engagementFunctional Assessment Questionnaire score <9 [97,98]: functional independence and ability to participate meaningfullyEnglish fluency and literacy: data validity (all measures are validated for use in English) and delivery modalityAbility and willingness to participate via live video in group session: delivery modalityNo self-reported safety issues with initiating lifestyle changes during the study: safety of participants and validity
**Exclusion criteria and brief rationales**
Mild cognitive impairment, AD/ADRD, or other neurodegenerative disease: study confound (intervention targets early AD/ADRD risk; ability to participate meaningfully)Psychotropic medication (eg, antidepressant) change in <3 months: study confoundPsychosis, uncontrolled bipolar disorder, or uncontrolled substance dependence or abuse: study confound (safety of participants; treatment confound; can affect participants’ answers)Current self-report of suicidal ideation: participant safetySerious medical illness expected to worsen in 6 months (eg, cancer): study confound (serious medical illness may act as a third variable)Use of an activity watch to track physical activity or sleep in <3 months and unwillingness to stop using it for the duration of the program: treatment confoundMindfulness practice lasting >45 minutes per week or cognitive behavioral therapy in <3 months: treatment confoundSelf-reported step count >5000 per day or ≥30 minutes of exercise per day: study population (intervention targets increased activity among sedentary older adults)

### Recruitment and Enrollment

Our recruitment strategy incorporates a combination of hospital partnerships, community outreach, and internet-based recruitment methods. Through our preliminary studies, we developed partnerships with several MGB clinics that are directly involved in the care of older patients with SCD. The clinics represent expertise in geriatrics, geriatric psychiatry, neurology, neuropsychology, memory care, and integrative medicine. To promote the study within our hospital, we have engaged clinic leadership, presented in team meetings, and distributed our IRB-approved flyer to providers and clinic waiting areas. The flyer contains study contact information and a QR code to an eligibility self-screener. In addition, patients can contact the study through a hospital web-based recruitment platform (MGB Rally). We aim to maximize the inclusion of older adults from diverse and underserved backgrounds to address disparities in AD/ADRD [99,100] and underrepresentation in prevention clinical trials [101,102]. First, we have proactively formed collaborations with MGB clinics that serve more diverse patients. Second, we have engaged community organizations and Councils on Aging (commonly known as “senior centers”) in Massachusetts. Community outreach consists of engaging community leadership, disseminating recruitment materials, and conducting public events (eg, networking nights and educational talks). We are specifically targeting outreach to underresourced communities of older adults in Massachusetts who face significant health disparities and heightened risk factors for AD/ADRD [103]. Third, we have consulted with our center’s Community Engagement Core on evidence-based recruitment strategies [104]. Fourth and last, we have expanded our outreach nationally via social media platforms, web-based study postings (eg, ClinicalTrials.gov and Alzheimers.gov), and articles and presentations developed for public audiences.

### Screening and Enrollment

The RA logs all referral information in a standardized REDCap (Research Electronic Data Capture; Vanderbilt University) [105] database. Participants have the option to complete an initial screening survey independently or by telephone with the RA. The RA contacts all potentially eligible participants to answer questions about the study, collect availability for groups, and assess technology access and readiness. Individuals who do not meet study criteria are offered resource sheets developed for older adults with SCD. The principal investigator ([name]) reviews all eligibility decisions and consults with the multidisciplinary study team if needed. After group times have been set, the RA meets with participants individually over Zoom to schedule the before the intervention assessments, review study technology, and obtain electronic informed consent via REDCap. The RA uses secure email to send confirmation and Zoom links for the before the intervention assessments.

### Assessments

#### Overview

Tables 1 and 2 detail the assessments and the frequency of data collection. All assessment data are stored in a REDCap database. An RA blinded to randomization reviews all measures for missing data, errors, or invalid responses.

**Table 1 table1:** Primary outcomes.

Construct and measure			Scoring		Criteria		Time point
**Feasibility**							
	Recruitment and enrollment	Percentage of individuals who participate and enroll from the total contacted		≥70%=good, ≥80%=excellent		Before the intervention	
	Outcome assessments	Percentage of participants with no missing outcome assessment data		≥70%=good, ≥80%=excellent		Before the intervention, after the intervention, and at 6-month follow-up	
	Garmin Vivosmart 5 watch	Percentage of participants who wore the watch at least 5 out of 7 days per week [106,107] for at least 10 hours a day [71]		≥70%=good, ≥80%=excellent		After the intervention	
	Daily surveys	Percentage of participants who completed at least 5 out of 7 daily surveys during the program		≥70%=good, ≥80%=excellent		After the intervention	

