#### Primary Analyses (Feasibility)

Statistical analyses will be performed in R (version 4.2.1; R Foundation for Statistical Computing) using RStudio (Posit Software, PBC) [202,203]. We will calculate frequencies and proportions to assess a priori feasibility Go–No-Go benchmarks for the feasibility, acceptability, appropriateness, credibility, satisfaction, and fidelity of the programs [64,70-74]. If these benchmarks are not met, revisions will be necessary before an efficacy trial. We will report benchmarks separately for the MHB intervention and HEP control groups.

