## Results

### Overview

This study was funded by a National Institute on Aging Mentored Patient-Oriented Research Career Development Award (K23; 1 K23 AG075257-01; September 2022). The study was approved by the IRB in October 2023. We began recruitment in January 2024. As of June 1, 2024, a total of 225 individuals had inquired about the study via self-referral or referral from a clinician or community partner. We made initial contact and conducted screenings with 213 (94.7%) of the 225 individuals; 25.6% (40/156) met the eligibility criteria. Of the 40 eligible participants, 21 (52.5%) were enrolled in 2 group cohorts, 17 (42.5%) were on hold for future group cohorts, and 2 (5%) withdrew before enrollment. Primary reasons for ineligibility included low AD/ADRD risk (CAIDE score <6; 54/116, 46.6%), active lifestyle (>5000 average steps per day and ≥30 minutes of exercise per day; 26/116, 22.4%), no self-reported SCD (18/116, 15.5%), age <60 years (16/116, 13.8%), regular mindfulness practice (8/116, 6.9%), and clinically significant cognitive impairment (Telephone Interview for Cognitive Status score <31 out of a maximum possible 41 points; 5/116, 4.3%).

All 21 enrolled participants were randomized to MHB (n=11, 52%) or the HEP (n=10, 48%) across 2 group cohorts (cohort 1: n=9, 43%; cohort 2: n=12, 57%). All participants completed before the intervention assessments. No participants have dropped out after enrollment. All participants in our first cohort completed ≥6 out of 8 sessions of either MHB or the HEP (including minimal makeup sessions) and after the intervention assessments (9/9, 100%). One participant requested to skip the HEP session on substance use due to a traumatic family history. The intervention for our second cohort (12/21, 57%) is ongoing (5 out of 8 sessions completed; 100% attendance with minimal makeup sessions). Across both cohorts, adherence rates are high for the Garmin Vivosmart 5 (128/147, 87.1% total weeks) and daily surveys (105/122, 86.1% total weeks). We plan to complete enrollment by December 2024 and data analyses by December 2025.

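### The recruitment benchmark (at least 70% of those contacted enroll) cannot be met on any screening count the article reports, because its denominator is left undefined

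*Protocol article*

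**What the plan says.** Table 1 (Primary outcomes, Feasibility) scores recruitment and enrollment as "Percentage of individuals who participate and enroll from the total contacted", with the criteria "≥70%=good, ≥80%=excellent". The Benchmarks section places these markers among the a priori Go–No-Go benchmarks that form the primary outcomes. The Objectives fix the sample: "We are enrolling 50 older adults (aged ≥60 y) with SCD and modifiable AD/ADRD lifestyle risk factors".

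The Results (Overview) give the recruitment position at 1 June 2024. By then "a total of 225 individuals had inquired about the study via self-referral or referral from a clinician or community partner". Of these, "We made initial contact and conducted screenings with 213 (94.7%) of the 225 individuals; 25.6% (40/156) met the eligibility criteria". Of the 40 eligible people, 21 were enrolled, 17 were on hold for later cohorts and 2 had withdrawn before enrollment. The reasons for ineligibility are tabulated out of 116.

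The Screening and Enrollment section uses the verb *contact* in a narrower sense, for the research assistant's approach to people who look potentially eligible. It gives no count for that group.

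On consequences, Primary Analyses (Feasibility) states: "If these benchmarks are not met, revisions will be necessary before an efficacy trial".

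**The concern.** A feasibility benchmark is useful only if it could be either met or missed, and if a miss points to something that can be acted on. Here the numerator is capped by design at 50, while the denominator grows with every person the team reaches. Recruitment is deliberately broad, covering clinics, community organizations, web platforms and national postings. Each ineligible person who responds and is contacted therefore lowers the score, although the Discussion counts the volume of inquiries as a success.

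If the row is applied as written, a primary benchmark is missed by a wide margin and the revision clause applies, without showing whether eligible people decline to join. If it is reinterpreted when the results are written up, the denominator will have been chosen after the counts were known. Either outcome weakens a set of primary outcomes whose value lies in having been fixed beforehand.

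**Working it through.** **Inputs**
- Threshold: 70% good, 80% excellent (Table 1).
- Planned enrollment: 50 (Objectives).
- Inquiries 225; contacted and screened 213; eligible 40 of 156; ineligible 116; enrolled 21; on hold 17; withdrew before enrollment 2 (Results, Overview).

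**The plan's own figure.** The Power Analysis claims more than 80% power to confirm all of 10 independent criteria with 50 participants if 82% meet each one. Taking the cut-off as 35 of 50 (70%), P(X ≥ 35 | n = 50, p = 0.82) = 0.988, and 0.988 to the tenth power, before rounding, is 0.886. The claim reproduces. It treats each criterion as a proportion of the 50 participants, however, and the recruitment row has a different denominator, so the calculation does not describe that row. The article does not list its ten criteria.

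**Current value.** 21/213 = 9.9%. Adding all 17 on hold: 38/213 = 17.8%.

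**Ceiling at full enrollment.** After the 17 on hold, 50 − 38 = 12 more are needed. The highest ratio arises if all 12 come from people already contacted: 50/213 = 23.5%. If they come instead from the 225 − 213 = 12 inquirers not yet contacted, it is 50/225 = 22.2%.

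**Ceiling on the smallest reported count.** 50/156 = 32.1%. This is generous: only 40 of those 156 are eligible, so the remaining 12 must come from outside the 156, giving 50/(156 + 12) = 29.8%.

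**What 70% would require.** With 50 enrolled, 50/0.70 = 71.4, so at most 71 contacts. With 213 contacted, 0.70 × 213 = 149.1, so 150 enrolled. Even without the cap of 50, solving (21 + x)/(213 + x) = 0.70 gives x = (149.1 − 21)/0.30 = 427 further contacts, every one of whom would have to enroll.

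**How much is ineligibility?** 40 + 116 = 156, so 213 − 156 = 57 contacted people have no reported eligibility outcome. Removing all 116 known ineligibles leaves 213 − 116 = 97. Then 38/97 = 39% and 50/97 = 52%, both still below 70%. Documented ineligibility explains much of the shortfall but not all of it.

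**With eligible people as denominator.** 21/40 = 52.5% if the 17 on hold count as not enrolled; 38/40 = 95% if all of them enroll. Leaving them out gives 21/23 = 91%, on the assumption that the 2 who withdrew had been offered a place. The 70% mark is within reach, but the value depends on how those on hold are counted.

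**The case against.** The strongest reply is that the article never says contacted means all 213. The Screening and Enrollment section reserves the verb for potentially eligible people, and on that reading the benchmark might be attainable. This stands in part: the term is ambiguous. But the article gives no number for the narrower group and does not link it to Table 1. Where it does attach a number to contact, it is "We made initial contact and conducted screenings with 213 (94.7%) of the 225 individuals". If the narrower meaning was intended, the row must say so, and that too means rewriting it.

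A second reply is that yield per contact is legitimate information for planning a larger trial. That is true, and it is a reason to keep reporting the figure. It does not justify a 70% pass mark that the figure cannot reach.

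A third is that 225, 213 and 156 are different quantities (inquiries, contacts, people with an eligibility result), so they do not contradict one another. That is fair. What remains is the unexplained step from 213 screened to "25.6% (40/156) met the eligibility criteria", which leaves the 57 unaccounted for.

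Three stronger readings are tempting and not supported:
- A reader might infer that the trial must now return No-Go. The only stated consequence of missing benchmarks is revision before an efficacy trial; no rule combines the rows into one decision, and a statement about power to confirm all benchmarks is not such a rule.
- A reader might infer that strict eligibility criteria are the sole cause. The 57 people without a reported outcome may be pending, unreachable, uninterested or ineligible.
- A reader might infer that willingness among eligible people is shown to exceed 90%. The 91% and 95% figures depend on the treatment of those on hold; counting all 40 now gives 52.5%.

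**Conclusion.** The concern holds for the row as literally written. With enrollment planned at 50 and 213 people already contacted, the benchmark cannot exceed 23.5% against a threshold of 70%, and no screening count in the article changes that: the most generous gives 32.1%. The conclusion rests on two assumptions: that enrollment stops at the planned 50, and that the denominator is one of the reported counts. It would fail only under a narrower, unreported definition of contacted covering no more than 71 people.

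This is more than a detail left to a fuller document, because following the stated rule gives a certain and largely uninformative miss on a primary benchmark and brings the revision clause into play. It does not settle the trial's overall decision, and it affects no comparison between the arms.

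**What to change.** Rewrite the recruitment row of Table 1 so that the denominator is eligible individuals offered a place in a cohort and the numerator is those who enroll. People on hold enter the denominator only once a place has been offered.

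Report two further figures descriptively, without a pass mark: the proportion enrolled among all contacted, as the row now defines it, and the screening yield (eligible over screened) on one fixed denominator, with the 57 people accounted for. Say in Primary Analyses (Feasibility) what a single missed benchmark implies.

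Date the change, record it in the registry entry, and disclose that it was made after interim counts had been seen.

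The work is one table row, a sentence and a registry note. The real cost is a post-launch change to a primary benchmark, made when the new quantity already looks favorable on some counts. The 70% and 80% cut-offs were also set for a different quantity, so keeping them needs a stated reason. Continuing to report the proportion under the present definition lets readers judge the change for themselves.
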